**Timing of outcomes assessment**

- Preliminary screening
- Review of inclusion and exclusion criteria
- Informed consent obtained
- Demography
- Family and medical history
- Prior and concomitant medications
- Randomization and group assignment

**Baseline evaluation (Day 1)**

- Clinical assessment
- Neurophysiological assessment

**Post-treatment evaluation (Day 168-week 24)**

- Clinical assessment
- Neurophysiological assessment

**Screening Phase**

At or before Visit 1, the study will be explained to the patient and caregiver. In the screening phase, all patients will undergo an extensive clinical investigation, including interviews on their medical history, a full neurological examination, the CDR-FTD, a complete blood screening, neuropsychological assessment, neuropsychiatric evaluation, and magnetic resonance imaging. In the 30 days before entering the study, subjects will have to be clear of treatment with any drug inducing modulatory effects on the cerebral cortex excitability, such as antidepressants, benzodiazepines, anti-epileptic drugs, or neuroleptics. All the patients will perform lumbar puncture for CSF biomarkers analysis for diagnostic purposes and to rule out AD pathology (Dubois et al., 2014) and a [18F] fluorodeoxyglucose (FDG) PET scan to evidence atrophy/hypometabolism.

All participants will sign a written informed consent after receiving an extensive disclosure of the experimental details.

**Evaluation Phase**

During the week before starting PEA-LUT administration, and during the week at the end of 4th (W4), 12th week (W12) and 24th week (W24) FTD patients will undergo clinical assessment. Neurophysiological assessment will be performed at baseline and W24 and the evaluation will be done in two different days.

1) Clinical Assessment: before and after the 24 weeks of treatment FTLD-CDR SoB, FAB, MMSE, SAND, ACE-R, FBI, ADCS-ADL, FAB and NPI will be administered.

2) Neurophysiological assessment: for TMS-EEG recordings, a TMS-compatible EEG equipment will be used for recording EEG activity from the scalp (BrainAmp, BrainProducts). The EEG will be continuously acquired from 61 scalp sites positioned according to the 10-20 International System. TMS-EEG recordings will be performed over the right and left DLPFC. To precisely position the coil over the cortical sites across different sessions, a neuronavigation system (Softaxic, E.M.S.) will be used. During the TMS-EEG session, DLPFC will be stimulated with 80 single TMS pulses (Koch et al., 2018).

**Treatment Phase**

After recruitment and baseline assessments, FTD patients will be assigned to PEA-LUT or PLC. We will use the Glialia® 700 m+70 mg oral sachets administered twice every day. The first mechanism of action for PEA was proposed by Rita Levi‐Montalcini's research group, who suggested that PEA acts via ‘Autacoid Local Injury Antagonism (ALIA)’ to down‐regulate mast cell activation (*Levi‐Montalcini et al., 1996*). Later, the existence of a ‘direct receptor‐mediated mechanism’ was proposed, and several studies demonstrated that PEA can act via direct activation of at least two different receptors: the PPAR‐α (*Lo Verme et al., 2005a*) and the orphan GPCR 55 (GPR55) (*Ryberg et al., 2007*). It was originally thought that PEA could also be a CB2 receptor agonist (*Facci et al., 1995*), but subsequent studies revealed that PEA has only very weak affinity for this receptor, explaining why some of its anti‐inflammatory effects are not blocked by CB2 receptor antagonists (*Costa et al., 2002*). As a result, the theory of the ‘entourage’ effect was put forward to raise the possibility that PEA could produce indirect receptor‐mediated effects (De Petrocellis et al., 2001; Di Marzo et al., 2001; Ho et al., 2008). For example, PEA, through the inhibition of the expression of FAAH, the enzyme responsible for the degradation of the endogenous cannabinoid receptor ligand (or endocannabinoid), anandamide (AEA) (*Di Marzo et al., 2001*), may indirectly activate CB2 and CB1 receptors (*Di Marzo et al., 2001; Petrosino et al., 2016a*). Likewise, PEA can indirectly activate the transient receptor potential vanilloid receptor type 1 (TRPV1) channels, which are also targets for the endocannabinoids (*Zygmunt et al., 1999, 2013*). In addition, PEA is also able to increase AEA‐ or 2‐AG‐induced TRPV1 activation and desensitization (*De Petrocellis et al., 2001; Di Marzo et al., 2001*; *Petrosino et al., 2016a*). More recently, it has also been demonstrated that PEA can activate TRPV1 channels or increase the expression of CB2 receptors via PPAR‐α receptors (*Ambrosino et al., 2013; Ambrosino et al., 2014*). In summary, these results suggest that PEA does not operate through just one main mechanism of action. Instead, synergistic interactions among several mechanisms often seem necessary so that PEA can produce its important therapeutic effects, acting on neuroinflammation, both in the central and the peripheral nervous system. All treatments will be administered for 24 weeks with no interruptions. The placebo sachets packaging will be identical to the PEA-LUT sachets.

**SECTION 1.7: STUDY POPULATION**

Eligible patients will be males and females with probable Frontotemporal Dementia according to current diagnostic criteria (Rascovsky et al., 2011, Gorno-Tempini et al. 2011) as specified in the entry criteria that follow. Entered patients who meet all of the inclusion criteria and are not excluded by any of the exclusion criteria will be randomized and proceed to Evaluation Phase.

**Inclusion Criteria**

Patients are eligible to be included in the study only if they meet all of the following criteria:

1. The patient has a diagnosis of probable Frontotemporal dementia based on the International consensus clinical diagnostic criteria described by Rascovsky et al., 2011, Gorno Tempini et al.2011.
2. The patient is a man or a woman, aged from 40 to 85 years.
3. The patient has a Clinical Dementia Rating-FTD (CDR-FTD) total score of ≤2 at Screening.
4. The patient has not been treated with acetylcholinesterase inhibitor (AChEI), i.e., donepezil, galantamine, or rivastigmine, at the time of screening.
5. The patient is able to comply with the study procedures in the view of the investigator.
6. Evidence of frontotemporal hypometabolism at PET imaging.
7. Evidence of amyloid markers excluding Alzheimer's disease (cerebrospinal fluid Abeta/Tau dosages or amyloid PET imaging).
8. The patient (or if applicable the legally acceptable representative if different from the responsible caregiver) and the responsible caregiver have signed the Informed Consent Form.
9. Has at least one identified adult caregiver who is able to provide meaningful assessment of changes in subject behavior and function over time and provide information on safety and tolerability, and is able to verify daily compliance with study drug

**Exclusion Criteria:**

1. Significant neurodegenerative disorder of the central nervous system other than FTD e.g., Alzheimer's disease, Lewy body dementia, Parkinson's disease, multiple sclerosis, progressive supranuclear palsy, normal pressure hydrocephalus, Huntington's disease, any condition directly or indirectly caused by Transmissible Spongiform Encephalopathy (TSE), Creutzfeldt-Jakob Disease (CJD), variant Creutzfeldt-Jakob Disease (vCJD), or new variant Creutzfeldt-Jakob Disease (nvCJD)
2. Significant intracranial focal or vascular pathology seen on brain MRI scan within a maximum of 6 months before Baseline leading to a diagnosis other than probable FTD.
3. The patients has history of seizure (with the exception of febrile seizures in childhood).
4. Metal implants in the head (except dental), pacemaker, cochlear implants, or any other non-removable items that are contraindications to MR imaging.
5. Treatment currently or within 3 months before Baseline with any of the following medications: Typical and Atypical antipsychotics (i.e., Clozapine, Olanzapine); Antiepileptics drugs (i.e., Carbamazepine, Primidone, Pregabalin, Gabapentin); Antidepressants (i.e., Citalopram, Duolxetine, Paroxetine).

**Screening Procedures**

Eligibility of participants in the study will be based on the results of sequential screening procedures including medical history, physical examination, and neurological evaluation including MRI or PET scan. The screening period allows patients adequate time to decide whether they wish to participate in the study

**SECTION 1.8: TREATMENT**

**1.8.1. Treatments administrated**

Treatment is given to all patients for 24 weeks with no interruption.

The investigational drug o-ultramicronized PEA-LUT (Glialia) is provided as oral sachets.

Placebo is identical in appearance and will be contained in identical packages

At each post-Baseline visit during the treatment period, the number of sachets dispensed to the patient/caregiver is recorded. Patient compliance with prescribed study drug is also assessed at each visit by questioning the patient and caregiver. Compliance data, including dates of any dose deviations and/or interruptions, and any other pertinent information are recorded in the source documentation.

Use of the following treatments are not allowed in combination with study treatment, due to confounding of efficacy and/or potential interaction with study treatment:

- Any investigational drug: disallowed <60gg from screening

- General anesthetics are disallowed during the study except in case of emergency procedures requiring anesthesia. Episodic use of local anesthetics is allowed.

- Antidepressant: stable treatment with no modification of dose with selective serotonin reuptake inhibitors (SSRIs), venlafaxine, moclobemide and mirtazapine for at least 3 months prior to the Screening Visit acceptable. Paroxetine and duloxetine should be used with caution. Dose modifications and initiation of treatment not allowed during the study.

- Antiparkinsonian agents (e.g., levodopa, dopamine agonists, COMT inhibitors, amantadine, monoamine oxidase B inhibitors, anticholinergics etc.): disallowed for 6 months prior to screening and during the study.

- Antipsychotics typical and atypical: disallowed for 3 months prior to screening and during the study.

- Sedative/hypnotics: disallowed for 3 months prior to screening and during the study. Melatonin will be allowed anytime.

**SECTION 1.9. EFFICACY AND SAFETY EVALUATIONS: OUTCOME MEASURES**

**Primary Efficacy Measure**

**1)** Global disease severity [Time Frame: change from baseline to Week 24]: Clinical Dementia Rating Scale- Frontotemporal dementia Sum of Boxes. The scores range from 0-24 with a higher score meaning higher disease severity. A modification in the pre-specified primary endpoint was done in this version based on upcoming literature findings (*Staffaroni et al., 2019; Desmarais et al 2019*). Indeed, emerging evidence suggests that, for trials potentially involving patients with any of the FTD syndromes, priority should be given to functional and global composite measures. These measures take into account the diverse manifestations of these disorders and are consider more attractive clinical outcome metrics due to their ability to yield comparable sample size estimates across all groups and their inherent clinical significance (Staffaroni et al., 2019; Desmarais et al., 2019). On the contrary, NPI should not be regarded as a reliable measure in this syndrome (Knopman et al., 2008; Staffaroni et al., 2019), possibly due to the inter-subject variability of behavioral phenotypes (Ranasinghe et al., 2016). The decision to prioritize CDR plus NACC FTLD - SoB was made by the Principal Investigator ([name]) independently of trial data and prior to unblinding.

**Secondary Efficacy Measures**

**1)** Activities of daily living [Time Frame: change from baseline to Week 24]: AD Cooperative Study - Activities of Daily Living (ADCS-ADL). The ADCS-ADL includes 23 items that were derived from a larger set of items describing performance of activities of daily living (ADL) by AD patients (*Galasko et al., 1997*). The ADCS contained 23 items covering physical and mental functioning and independence in self-care. For each basic ADL (eating, walking, toileting, bathing, grooming, selecting, clothes), there is a forced choice of best response. All other ADL consist of a main question followed by subquestions (descriptors). The scores range from 0 to 78, with lower values indicating greater disability.

**2)** Neuropsychiatric evaluation [Time Frame: change from baseline to Week 24]: Neuropsychiatric Inventory (NPI). The NPI assesses behavioral disturbances in dementia. The NPI is reliable and valid (*Cummings, 1994*) and has been reported to be sensitive to the effects of tacrine (*Kaufer et al., 1996*). The NPI measures the following behavioral areas: delusions, hallucinations, agitation, depression, anxiety, euphoria, apathy, disinhibition, irritability, aberrant motor behavior, night time behaviors, and eating disorders. Symptoms are rated in terms of frequency (0-4) and severity (0-3). Total score range is 0-144, where higher scores indicate higher behavioral psychopathology.

**3)** Neuropsychiatric evaluation [Time Frame: change from baseline to Week 24]: Frontal Behavioural Inventory (FBI). The scores range from 0-72 with a higher score meaning more severe behavioural disturbances.

**4)** Frontal cognitive functions [Time Frame: change from baseline to Week 24]: Frontal assessment battery (FAB). The Frontal Assessment Battery is a brief screening tool for the assessment of frontal lobe function *(Appollonio et al., 2005*). It is used to measure abstraction, fluency, impulsivity and primitive reflexes in patients who have a suspected frontal lobe deficit. A higher score indicates better performance. The FAB has been used to assess the effects of rivastigmine on frontal functions in AD patients (*Park et al., 2017*).

**5)** Language function evaluation [Time Frame: 24 weeks ] Screening for aphasia in Neurodegeneration (SAND) scale (*Catricalà et al., 2017*) . The scores range from 0-84 with a higher score meaning less severe language deficits.

**6)** Global Cognition [Time Frame: change from baseline to week 24]: Addenbrooke's Cognitive Examination Revised (ACE-R)The scores range from 0-100 with a higher score meaning less cognitive impairment.

**7)** Global Cognition [Time Frame: change from baseline to week 24]: Mini Mental State Examination (MMSE). The scores range from 0-30 with a higher score meaning less cognitive impairment.

**8)** TMS-evoked EEG responses, in terms of potentials (i.e., TEPs) and oscillations (i.e., TRSP) as a novel probe of cortical excitability changes induced by PEA-LUT. TEPs and TRSP will be computed by stimulating the left and right DLPFC and simultaneous electroencephalography recordings over all the scalp.

**1.9.1 SAFETY EVALUATIONS**

Investigators are responsible for monitoring the safety of patients who have entered this study. The investigator is responsible for the appropriate medical care of patients during the study. The investigator remains responsible for following, through an appropriate health care option, AEs that are serious or that caused the patient to discontinue before completing the study. The patient should be followed until the event is resolved or explained. Frequency of follow-up evaluation is left to the discretion of the investigator.

**1.9.2.1 Adverse Events and Other Safety Measures**

A clinical study AE is any untoward medical event associated with the use of a drug or drug delivery system in humans. AE collection begins after the patient has signed informed consent and has received study drug. If a patient experiences an AE after signing informed consent, but before receiving study drug, the event will not be collected unless the investigator feels the event may have been caused by a protocol procedure.

At each clinic visit, AEs will be recorded, vital signs will be measured and physical and neurological examination will be performed. An independent Data Monitoring Committee will monitor the patients' safety according to the Data Monitoring Committee Charter.

**SECTION 1.10. INFORMED CONSENT, ETHICAL REVIEW AND REGULATORY CONSIDERATIONS**

**1.10.1 Informed Consent**

The principal investigator is responsible for ensuring that the patient understands the potential risks and benefits of participating in the study, including answering any questions the patient may have throughout the study and sharing in a timely manner any new information that may be relevant to the patient’s willingness to continue his or her participation in the trial. The Informed Consent Form (ICF) will be used to explain the potential risks and benefits of study participation to the patient/caregivers in simple terms before the patient is entered into the study, and to document that the patient is satisfied with his or her understanding of the risks and benefits of participating in the study and desires to participate in the study. The investigator is responsible for ensuring that informed consent is given by each patient or legal representative. This includes obtaining the appropriate signatures and dates on the ICF prior to the performance of any protocol procedures and prior to the administration of investigational product.

**1.10.2 Ethical Review and Regulatory Considerations**

This study will be conducted in accordance with:

1) consensus ethics principles derived from international ethics guidelines, including the Declaration of Helsinki and Council for International Organizations of Medical Sciences (CIOMS) International Ethical Guidelines

2) Institutional Review Board (IRB) Guidelines

3) Applicable laws and regulations.

The investigator or designee will promptly submit the protocol to applicable ERB. An identification code assigned by the investigator to each patient will be used in lieu of the patient’s name to protect the patient’s identity when reporting AEs and/or other trial-related data.

**1.10.3 Investigator Information**

Physicians with expertise in neurology or geriatrics who have clearly documented extensive experience in AD and FTD trials will participate as investigators in this clinical study. In addition, licensed clinicians (neuropsychologists) who have clearly documented extensive experience in AD and FTD trials may participate as investigators in this clinical study. Cognitive assessments must be administered by an individual trained in the use of these instruments. Neurophysiological recordings and analysis must be performed by experts in this field. All lumbar punctures must be performed by an appropriately trained individual.

**2. STATISTICAL ANALYSIS PLAN**

**2.1. Determination of Sample Size**

The appropriateness of our sample size, i.e. 48 randomly assigned patients (25 to PEA- LUT treatment group and 23 to placebo group), was based on the effect size obtained in a preliminary study by our group using a shorter version of our protocol. Considering the cognitive and behavioural results of this study, we obtained a medium effect size of 0.93 (computed as the difference between the post-treatment and the pre-treatment mean over the pooled standard deviation). With these effect sizes, adopting a two-tailed paired Wilcoxon signed-rank test, with type I error alpha=0.05, the minimum sample for reaching a power (1-β) of 0.95 was estimated equal to n=18 patients per group. We decided to increase our sample size at least of 30% considering possible drop-outs.

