Based on this premises we recently performed a pilot study to investigate the efficacy and safety of PEA-LUT at the oral dosage of 700 mg x 2/day in a sample of 18 newly diagnosed FTD patients evaluated with clinical and behavioral\cognitive scales at baseline and after one month of treatment PEA-LUT. Patients were evaluated at baseline and after one month of treatment with PEA-LUT with the following scales: NPI, MMSE, FAB, ADL/IADL, FTLD-CDR SoB. We observed a significant amelioration in the behavioral symptoms as measured by changes from baseline in the NPI mean score (pre:15.87±4.01 vs post: 8.50±1.99; p=0.018). Moreover, we found surprisingly an improvement in frontal executive functions as revealed by an improvement in the FAB score (pre: 6.4±1.54 vs post: 7.95±1.56; p=0.038). There was also a trend for amelioration in the MMSE (pre: 18.6±3.34 vs post: 19.6±3.33; p=0.23). To non-invasively assess intracortical circuits of the primary motor cortex (M1), we used paired-pulse transcranial magnetic stimulation (ppTMS) (*Kujirai et al., 1993; Ziemann et al., 1996*). Specifically, we investigated short interval intracortical inhibition (SICI) to investigate GABA(A)-ergic neurotrasmission; short interval intracortical facilitation (ICF), to investigate glutamatergic neurotransmission and long interval intracortical inhibition (LICI), to investigate GABA(B)-ergic neurotransmission. We also investigated short latency afferent inhibition (SAI), which reflects cholinergic neurotransmission (*Tokimura et al., 2000*). Finally, to probe plasticity mechanisms, we used a novel form of TMS, namely theta-burst stimulation (TBS), to induce long-term potentiation (LTP) of M1. These measures have been evaluated by means of motor-evoked potentials (MEPs), a well-known index of corticospinal excitability (*Barker et al., 1985*).

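### The planning effect size of 0.93 cannot be derived from the reported pilot figures, and the 95% power built on it does not apply to the between-arm comparison of FTLD-CDR SoB

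*Combined protocol and SAP*

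**What the plan says.** SAP section 2.1 bases the sample on a preliminary study by the same group. It opens the derivation with "Considering the cognitive and behavioural results of this study" and reports: "we obtained a medium effect size of 0.93 (computed as the difference between the post-treatment and the pre-treatment mean over the pooled standard deviation". It does not say which scale or combination of scales gave 0.93. With a two-tailed paired Wilcoxon signed-rank test, alpha 0.05 and power 0.95, it arrives at 18 patients per group. It then adds at least 30% for dropout and reports 48 randomised patients (25 and 23).

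The pilot is described in section 1.4: 18 newly diagnosed patients, all treated, assessed at baseline and at one month on "the following scales: NPI, MMSE, FAB, ADL/IADL, FTLD-CDR SoB". Numbers are given for three of these scales:

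- NPI: "pre:15.87±4.01 vs post: 8.50±1.99; p=0.018"
- FAB: "pre: 6.4±1.54 vs post: 7.95±1.56; p=0.038"
- MMSE: 18.6±3.34 before, 19.6±3.33 after, p=0.23

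No pilot result is given for ADL/IADL or FTLD-CDR SoB. The text does not say whether ± is an SD or a standard error, which test produced the p-values, or how many patients contributed to each scale.

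Section 1.5 makes FTLD-CDR SoB at 24 weeks, PEA-LUT against placebo, the primary outcome, analysed by a mixed model. Section 1.9 records that this was a change: "A modification in the pre-specified primary endpoint was done in this version based on upcoming literature findings". Section 2.1 contains no calculation for that endpoint.

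**The concern.** A reader takes section 2.1 to mean that the trial has 95% power for its primary comparison. That needs two things. The input of 0.93 should be recoverable from the pilot, and it should describe the quantity the trial tests. The three reported scales do not give 0.93 by the stated formula. The input also differs from the primary comparison in endpoint, duration and type of contrast: a change within one treated group rather than a difference between arms.

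The interpretation of the result is at stake. If the primary is not significant, the plan offers no sound basis for saying what FTLD-CDR SoB difference the trial could have detected.

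**Working it through.** **1. The plan's own figure.** Inputs from SAP 2.1: effect 0.93, two-sided alpha 0.05, power 0.95, paired Wilcoxon signed-rank test. Noncentral-t power for a paired test with Wilcoxon efficiency 3/π (normal differences) is 0.951 at n = 18. Simulation of the exact signed-rank test gives 0.954 at n = 18 and 0.936 at n = 17. So 18 reproduces. The allowance also fits: 18 × 1.3 = 23.4, so 24 per group and 48 in total. The fault is in the input, not in this step.

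**2. The stated formula applied to the reported pilot.** d = |post − pre| / √((SD_pre² + SD_post²)/2), with ± read as SD:

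| Scale | Difference | Pooled SD | d |
|---|---|---|---|
| NPI | 15.87 − 8.50 = 7.37 | √((4.01² + 1.99²)/2) = 3.17 | 2.33 |
| FAB | 7.95 − 6.4 = 1.55 | √((1.54² + 1.56²)/2) = 1.55 | 1.00 |
| MMSE | 19.6 − 18.6 = 1.00 | √((3.34² + 3.33²)/2) = 3.34 | 0.30 |

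The mean of the three is 1.21 and the median 1.00. Pairwise means are 1.66, 1.31 and 0.65. With the baseline SD as divisor, the values are 1.84, 1.01 and 0.30. None is 0.93.

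A paired test also works with the SD of the differences, not the pooled SD. With equal SDs, the paired effect is d/√(2(1 − r)), which equals d only when the pre-post correlation r is 0.5. No correlation is given.

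**3. Other readings, each conditional.**

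- If ± is a standard error and n = 18 on each scale, each d is divided by √18 = 4.24, which gives 0.55, 0.24 and 0.07.
- If the p-values come from paired t-tests with n = 18 on each scale, then t(17) = 2.618, 2.250 and 1.245. Dividing by √18 gives paired effects of 0.62, 0.53 and 0.29.

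The documents state none of these conditions.

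**4. Power for a between-arm comparison.** Two-sample t-test, two-sided 0.05, noncentrality d/√(1/n1 + 1/n2). With d = 0.93:

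- 18 and 18: power 0.774
- 25 and 23: power 0.883
- 95% power would need 32 per arm

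No FTLD-CDR SoB effect is given, so other between-arm values can only be assumed. With 25 and 23 complete, power is 17% at d = 0.30, 40% at 0.50 and 77% at 0.80.

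**5. Detectable difference with 25 and 23 complete.** Solving the same formula for d gives 0.83 at 80% power and 0.96 at 90%.

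**The case against.** Several points on the other side stand.

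- Section 2.1 refers to the pilot results collectively and goes on to speak of effect sizes in the plural, so 0.93 may be a summary across scales. A fourth effect of 0.09 would bring a four-scale mean to (2.33 + 1.00 + 0.30 + 0.09)/4 = 0.93. The right statement is therefore that 0.93 cannot be derived from what is reported, not that it is wrong. The adjective medium may simply be meant as mean; nothing turns on it.
- The planned analysis is a mixed model over several visits, so a two-sample t-test only approximates its power.
- The 48 patients are reported as already randomised, so the point cannot change N.

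A reader might go further and infer that the ± values cannot be SDs. With 18 patients, the SD of the NPI change could be at most 4.01 + 1.99 = 6.00, so a paired t would be at least 7.37/(6.00/√18) = 5.21, far from p=0.018. The documents do not support that conclusion, because it needs a paired t-test and 18 analysed patients, and neither is stated. There is a sign that fewer contributed. NPI totals are whole numbers, and no total over 18 patients gives a mean of 15.87 (285/18 = 15.83, 286/18 = 15.89). As an example only, eight patients would give 127/8 = 15.875 and 68/8 = 8.50, the first matching if truncated. Seven non-zero changes, all in one direction, give an asymptotic Wilcoxon p of 0.018. The implied paired effect also moves with n: under a paired t-test, p=0.018 corresponds to 0.62 with n = 18, 0.91 with n = 10 and 1.09 with n = 8.

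**Conclusion.** The point holds in two parts. First, 0.93 is not traceable to the pilot results in the protocol: the stated formula gives 2.33, 1.00 and 0.30 with ± as SD. Second, and more important, the 95% power does not apply to the primary comparison. It belongs to a one-month within-group change on unnamed cognitive and behavioural scales, whereas the primary is a 24-week difference between arms on FTLD-CDR SoB. The pilot administered that scale, but the documents give no result for it and no planning difference or SD.

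If 0.93 is granted as a between-arm effect, power is about 77% with 18 per arm and 88% with 25 and 23 and no missing outcomes. These figures assume a simple two-sample t-test. They illustrate the gap and do not estimate the power for FTLD-CDR SoB, which remains undocumented.

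Two stronger conclusions should not be drawn. One is that 0.93 is overstated against the pilot's own p-values; this depends on a paired t-test and n = 18 throughout. The other is a power figure obtained by using the p-value-implied paired effects of 0.62, 0.53 or 0.29 as between-arm effects. That adds the same conditions and treats within-group changes on other scales as differences between arms on the primary. The validity of the primary test and its type I error are not affected.

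**What to change.** In SAP 2.1, withdraw 0.93 and the 95% power as the justification for the primary endpoint. Then do one of the following:

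- Report the pilot change in FTLD-CDR SoB with its SD and number analysed, and state the power for the between-arm comparison on that scale, making clear that the pilot was uncontrolled and lasted one month.
- State that N was set by feasibility and give the detectable standardised between-arm difference with 25 and 23 complete: d = 0.83 at 80% power and 0.96 at 90%, by a simple two-sample approximation.

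If 0.93 is kept as history, name the scales and formula that produced it and correct or drop the word medium. In section 1.4, label the ± values as SD or standard error, and give the test and the number analysed for each scale.

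The cost is a change of wording plus one calculation from pilot data the investigators should hold, or none beyond the detectable difference above. The stated justification becomes less favourable. N and the primary analysis do not change.

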**SECTION 1.5: OBJECTIVES**

The study is designed to evaluate the efficacy and safety of Co-ultramicronized PEA-LUT administration at the oral dosage of 700 mg x 2/day for 24 weeks in newly diagnosed FTD patients. Fifty consecutive patients (40-85 years) will be recruited and will be randomized to PEA-LUT or placebo administration. To evaluate the cognitive effects of PEA-LUT we will use a battery of cognitive tests assessing global cognition, executive functions and behavior that will be performed at Baseline before starting treatment and repeated on-treatment at weeks 4, 12 and 24.

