**Primary objective:**

The primary objective of this study is to test the hypothesis that therapy with PEA-LUT could have a relevant clinical impact on global disease severity in FTD patients as compared with placebo. The primary objective will be evaluated using a study endpoint at 24 weeks after initiation of treatment. The primary objective will be assessed using a Generalized Linear Mixed Model (GLMM) for repeated measures on the primary outcome: FTLD-modified Clinical Dementia Rating scale Sum of Boxes (FTLD-CDR SoB), in which the specific hypothesis is that the global disease severity progression at the end of the treatment phase for PEA-LUT will be significantly less than that for placebo.

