**2.3 Statistical and Analytical Plans**

**2.3.1. General Considerations**

Unless otherwise noted, all tests of treatment effects will be conducted at a 2-sided alpha level of 0.05; 2-sided confidence intervals will be displayed with a 95% confidence level. All tests of interactions between treatment and other factors will be conducted at an alpha level of 0.05. All analyses will follow the intent-to-treat (ITT) principle unless otherwise specified. An ITT analysis is an analysis of data by the groups to which subjects are assigned by random allocation, even if the subject does not take the assigned treatment, does not receive the correct treatment, or otherwise does not follow the protocol.

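### The 95% power in SAP section 2.1 belongs to a one-group pre/post test, not to the PEA-LUT versus placebo comparison that is the primary hypothesis

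*Combined protocol and SAP*

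**What the plan says.** The whole sample size justification is in SAP section 2.1. The effect comes from a preliminary study: "we obtained a medium effect size of 0.93 (computed as the difference between the post-treatment and the pre-treatment mean over the pooled standard deviation". The test is specified as "adopting a two-tailed paired Wilcoxon signed-rank test, with type I error alpha=0.05". The result is that "the minimum sample for reaching a power (1-β) of 0.95 was estimated equal to n=18 patients per group". An allowance follows: "We decided to increase our sample size at least of 30% considering possible drop-outs". The sample is given as "48 randomly assigned patients (25 to PEA- LUT treatment group and 23 to placebo group".

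The primary objective in section 1.5 is a comparison between arms: "the global disease severity progression at the end of the treatment phase for PEA-LUT will be significantly less than that for placebo". SAP section 2.3.4 analyses each outcome with a mixed model containing group, time and their interaction, and section 2.3.1 adds that "all tests of treatment effects will be conducted at a 2-sided alpha level of 0.05".

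The only pilot described, in section 1.4, had 18 patients. All took PEA-LUT and all were assessed before and after one month.

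**The concern.** A paired signed-rank test asks whether one group changed from its own baseline. The trial asks whether change differs between two groups, so the contrast carries the sampling error of both arms. Eighteen patients sufficient for the first question are not thereby sufficient, per group, for the second.

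At stake is how the result is read. A stated power of 95% implies a 5% chance of missing the assumed effect. If the trial finds no significant difference, a reader relying on that figure would give the null result more weight than the design supports. It is also the SAP's only justification for the sample size.

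**Working it through.** **Inputs.** Effect 0.93, two-sided alpha 0.05, target power 0.95, 18 per group and 25/23 randomised (SAP 2.1); two-sided 0.05 for treatment tests (SAP 2.3.1). Power is from the noncentral t distribution. For the rank tests, n is multiplied by 3/π, their relative efficiency for normal data.

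**Step 1: reproduce the plan's figure.** For a paired test, the noncentrality is d·√n with n − 1 degrees of freedom.
- Paired t, n = 18: 0.93 × √18 = 3.95, power 0.960.
- Signed-rank, n = 18: 0.93 × √(18 × 3/π) = 3.86, power 0.951. At n = 17 it is 0.938.

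So 18 is the one-group paired answer. Simulating the signed-rank test gave 0.954 at n = 18 and 0.936 at n = 17.

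**Step 2: use the contrast the trial tests.** For two arms, the noncentrality is d·√(n₁n₂/(n₁+n₂)) with n₁ + n₂ − 2 degrees of freedom. Here 0.93 is taken as the between-arm standardised difference.
- 18/18: 0.93 × √(324/36) = 0.93 × 3 = 2.79.
- 25/23: 0.93 × √(575/48) = 3.22.

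| Evaluable per arm | t-test | Mann-Whitney |
|---|---|---|
| 18/18 | 0.774 | 0.753 |
| 25/23 | 0.883 | 0.868 |

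Simulation at 18/18 gave 0.778 and 0.749. The smallest equal arms reaching 0.95 are 32 (t-test) or 33 (Mann-Whitney).

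**Step 3: what Step 2 assumes.** The plan scales 0.93 by the pooled SD, not by the SD of the change. With pre/post correlation r and equal variances, the standardised change is 0.93/√(2(1 − r)). This equals 0.93 only when r = 0.5, so entering 0.93 in the paired test implies r = 0.5. The plan gives no r. With no placebo change, a t-test on change scores gives:

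| r (assumed) | Standardised change | Power 18/18 | Power 25/23 |
|---|---|---|---|
| 0 | 0.66 | 0.48 | 0.61 |
| 0.25 | 0.76 | 0.60 | 0.73 |
| 0.5 | 0.93 | 0.77 | 0.88 |
| 0.6 | 1.04 | 0.86 | 0.94 |
| 0.7 | 1.20 | 0.94 | 0.98 |

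**Step 4: can one r rescue both stated figures?** Power of 95% at 18/18 needs a standardised change of 1.237, so r = 1 − (0.93/1.237)²/2 ≈ 0.72. At that r the paired signed-rank calculation would have returned 12 patients, not 18. No single r gives both 18 from the paired test and 95% between arms at 18 per arm.

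**Step 5: placebo change.** An uncontrolled pre/post effect equals the arm difference only if placebo patients do not change. As an illustration only, if placebo change took away a quarter of the effect (0.93 × 0.75 = 0.70), 25/23 complete would give 66% power by t-test.

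**Step 6: detectable difference.** Solving the two-sample t formula for d at 25/23 complete gives 0.83 for 80%, 0.96 for 90% and 1.06 for 95% power.

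**The case against.** The strongest reply is that the planned analysis is not a two-sample test at one time point. It is a repeated-measures model over baseline and weeks 4, 12 and 24, and it can gain power from within-patient correlation. This stands as far as it goes: at r = 0.7, 25/23 complete would have 98% power on the Step 3 calculation. It rules out presenting 75-77% or 87-88% as the trial's actual power. It does not restore the 95% claim, because the plan neither states a correlation nor uses one in the sizing, and Step 4 shows that the stated figures cannot both hold for 18 per arm.

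A second reply is that any new percentage at 0.93 is as poorly grounded as the old one. That also stands. The effect comes from cognitive and behavioural results of a shorter version of the protocol. Section 1.4 lists FTLD-CDR SoB among the pilot scales but reports no result for it, and section 1.9 records that the primary endpoint was changed. This is why the remedy should rest on the detectable difference.

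Three further readings are tempting but unsupported:
- A reader might infer that the 30% increase was missed, because 18 × 1.3 = 23.4 and the placebo arm has 23. On the total it is met: 36 × 1.3 = 46.8, and 48/36 is a 33% increase. Simple randomisation (SAP 2.2) does not guarantee equal arms.
- A reader might infer an expected dropout of 30% and recompute power after that loss. The plan states an inflation for possible dropouts, not a dropout rate.
- A reader might see a contradiction between 48 in SAP 2.1 and "Fifty consecutive patients (40-85 years) will be recruited" in section 1.5. Section 1.6 makes the target approximate, and 25/23 reads like an achieved count (an inference) beside a recruitment target. This is a minor labelling point with no bearing on power.

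**Conclusion.** The point holds as a mismatch between the sizing test and the primary hypothesis. The plan's arithmetic is correct for the test it names; the error is in presenting the result as the power of a two-arm trial.

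If 0.93 is the between-arm difference, with no placebo change and r = 0.5 for change scores, the chance of missing it is about 23-25% at 18 evaluable per arm and 12-13% with all 48 evaluable, against the 5% implied. With r unstated, power at 18 per arm runs from about 48% (r = 0) to 94% (r = 0.7), below 95% throughout that range.

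A reader might conclude that the trial has been shown to be too small. The documents do not support that: they give neither the correlation nor an effect on the 24-week primary endpoint, so power for that endpoint is unknown.

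**What to change.** In SAP section 2.1, withdraw the 95% figure and replace the paired calculation with a between-arm one for the fixed sample. State the detectable standardised difference with 25 and 23 complete: about 0.83 at 80%, 0.96 at 90% and 1.06 at 95% power, two-sided alpha 0.05. Name the SD to which the difference is scaled.

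If power at 0.93 is quoted at all, give its assumptions alongside: no placebo change, the assumed pre/post correlation, and an effect taken from preliminary cognitive and behavioural results rather than from FTLD-CDR SoB at 24 weeks. Label 50 as the recruitment target and 48 as the number randomised, if that is what they are.

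The cost is wording only, and a less favourable stated figure. No extra patients are needed, and the analysis and alpha are unchanged.
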